## Abstract

**Background:**

Trauma-focused cognitive-behavioural treatments have been proven to be effective for reducing symptoms in female survivors of intimate partner violence (IPV), although they still present some difficulties (e.g. significant drop-out rates, low adherence). Based on existing evidence about the difficulty of accessing memories of positive experiences among these women, we considered integrating positive memory evocation in trauma-focused treatments. The present study aims to test the effect of adding a positive memory module to trauma-focused CBT for female survivors of IPV.

**Methods:**

The study is a single-blind, randomized controlled trial (RCT) comparing two trauma-focused CBT (with and without a positive memory module) for female survivors of IPV and a wait-list condition (superiority trial), including pretreatment and posttreatment measures, and follow-ups at 3, 6 and 12 months. Assessors of treatment outcome will be blinded to the trial arm. We aim to recruit 135 participants who will be randomized to one of the experimental conditions. The primary outcome is PTSD symptom severity. Secondary outcome measures include IPV, attitudes towards IPV, posttraumatic cognitions, centrality of trauma, self-concept, positive and negative affect, depression, anxiety, emotional dysregulation or health-related quality of life, as well as satisfaction with treatment. Moreover, adherence to and satisfaction with treatment will be considered.

**Discussion:**

This study first analyses the effect of including positive memory evocation into a trauma-focused treatment for female survivors of IPV. This strategy aims to improve the effect of the treatments and enhance the healing of the trauma by developing a more integrated and emotionally modulated autobiographical narrative that contributes to the recovery and well-being of the victims.

**Trial registration:**

ISRCTN73702156. Registered on 10 March 2022.

## Background

Various cognitive-behavioural treatments focused on trauma have been shown to be effective with a large number of trauma survivors [1, 2]; however, many clinical trials have intentionally excluded women who suffer intimate partner violence (IPV) (e.g. groups of Foa and Resick) for reasons such as alleging that they are treatments only for previous traumas rather than ongoing trauma [3]. Moreover, this lack of interest is related to a series of factors that affect the way in which these treatments can be applied to women who survive IPV and that hinder their accessibility to such treatments. Notably, the concurrence of a series of demands (e.g. protecting children, obtaining financial support, legal processes) that lead to the lack of time and money to follow a treatment or the fear that the aggressor will use against her the fact or following a psychological treatment (e.g. claiming that she is not able to take care of the children or use it as an excuse for the continuation of violence). In short, trauma-focused therapies for victims of IPV are neither desired nor accessible to all survivors. In addition, such therapies do not focus on many of the domains affected by long-term interpersonal trauma, such as IPV.

Until recently, the treatment of traumatic sequelae in women who are victims of continuous intimate partner violence has received little attention. In recent years, a series of reviews have been published focused on psychological interventions among survivors of IPV [3–7]. An analysis of these reviews allows us to identify three psychological intervention programs specifically focused on trauma for women survivors of IPV with contrasted evidence of their effectiveness for their application in a generalized manner (i.e. not focused only on groups of women with specific socioeconomic characteristics, sociocultural characteristics or comorbidities): (1) the Cognitive Trauma Therapy for Battered Women (CTT-BW), which was developed by the Kubany team [8–10]; (2) the Helping to Overcome PTSD through Empowerment (HOPE), which was developed by Johnson and Zlotnick [11] and Johnson et al. [12]; and (3) the Cognitive-Behavioural Treatment (CBT) for battered women with posttraumatic symptom [13, 14].

These three programs involve the application of brief (between 1 and 2 months of total duration) and multiple components interventions that offer a structured description of the treatments and that provide results on their effectiveness, thus highlighting the effect of the program on the reduction of posttraumatic and depressive symptoms over time. However, the analysis of these programs leads us to conclude, as did Warshaw et al. [3] or more recently Hameed et al. [7], that more research is needed to analyse the effectiveness of trauma-focused treatments for women survivors of IPV, especially if they are still being abused or if they are at risk of reabuse. It is important to remember that the treatments designed to reduce PTSD or trauma-related depression were originally created for unique traumatic events or traumatic experiences that occurred in the past and are unlikely to occur in the future. For many women, however, abuse or fear of future abuse is ongoing, regardless of their relationship with the abuser. In these circumstances, some of the components of the treatment may be particularly difficult to tolerate and may require modification. For example, “reliving” abuse through some form of exposure can potentially increase a woman’s discomfort rather than decrease it. Moreover, as Brewin [15] points out, traumatic events do not always involve fear but can be associated with other emotions (e.g. guilt, shame) that lead to differentiated patterns of symptoms. This situation, which frequently occurs among survivors of IPV, may require additional cognitive interventions to the standard treatment with exposure, something that is contemplated in the three programs mentioned.

The challenge, therefore, is to identify the essential elements for treatment while modifying the intervention to make it possible for women to participate and reduce the significant dropout rates (reducing the length, dose or frequency; incorporating additional specific elements…). Similarly, there is a clear need to identify the objectives and priorities of women and adapt treatment to them, including determining what makes it possible for women to be involved in treatment over time in a safe way and developing culturally specific approaches [3]. In addition, the question arises as to whether these treatments are aimed at the trauma recovery or the reduction of trauma symptoms (in fact, most studies measure the outcome by evaluating the effectiveness in reducing the symptoms of PTSD and depression). In this regard, several studies have shown the relationship between PTSD symptomatology and the risk of reabuse in IPV through symptoms of emotional dullness [16, 17]. From this point of view, adequate intervention on PTSD symptoms (particularly on dullness symptoms) would be imperative for the prevention of future reabuse [12].

In recent years, our research has been focused on the analysis of the characteristics of the narrative (and, therefore, of the memory) of women victims of intimate partner violence about the traumatic event they have experienced. The frame of reference for this approach is the cognitive model of trauma memory. The aim is to further develop efficient and effective intervention strategies adapted to the specific problems and needs of this type of victim. When analysing the relationships between the characteristics of the traumatic narratives and the evolution of the victims, it was found that the way in which they reported the trauma allowed the prediction of the development of different types of psychological symptoms [18, 19]. In summary, the results suggest that people who tend to re-experience the emotions linked to the traumatic event during the narrative show a greater immersion in the memory and present more severe symptoms of PTSD. Unfortunately, it is difficult to draw conclusions about the specific nature of the relationship between the way memory is represented and PTSD. It is unclear whether the emotional intensity linked to a memory is the cause of the development of symptoms or if it is the people with the worst evolution who re-experience their emotions more intensely. However, from the first formulations about the functioning of memory, there is the conviction that memory is a primarily constructive process where interpretation plays a crucial role. This implies assuming that memories are created and shaped through subsequent revaluations [20], so it is highly likely that traumatic memories and the emotional response to them are mutually reinforcing. Thus, individual differences in the ability to experience negative emotions with high intensity may be partly responsible for greater accessibility of traumatic memories. Rubin et al. [20] state that this accessibility can lead to frequent re-evaluations of the memory of the event, which can occupy a central place in the personal history of the individual. The high centrality given to the event will contribute, in turn, to maintaining its memory over time, as well as its emotional impact, thus facilitating continuous reassessments. In this way, centrality, accessibility and posttraumatic symptoms could form a vicious circle. The avoidance symptoms of PTSD will illustrate the unsuccessful efforts of the person to break this relationship and reduce the accessibility of traumatic memories.

The study also revealed that the emotional state of the victim is not only related to traumatic memories but also related to the way in which positive events are remembered. To date, narrative studies of PTSD have focused on analysing the content of traumatic memories, and the characteristics of happy memories have been taken into account mainly for comparative purposes. Fernández-Lansac and Crespo [18, 19] suggest that linguistic aspects of positive narratives (i.e. length and speed of speech) can more accurately predict the trajectory of victims than aspects related to the traumatic narratives themselves; differences have been observed in the characteristics of the memories of positive events between women who were victims of violence and women not exposed to trauma [21].

This finding may imply a change in approach by proposing that, although a good adjustment after the trauma depends largely on how the traumatic event is remembered, the way in which the rest of life events are remembered also plays a determining role. Additionally, the degree to which different types of memories compete in the construction of the personal history and identity of the victim can determine posttrauma outcomes. In this study, the impact of positive experiences on the biography of the participants was not studied, but it could be hypothesized that a greater centrality of these experiences would be associated with a better evolution. In fact, although Bernsten et al. [22] found no relationship between the centrality of positive events and the development of posttraumatic symptoms, other studies [23, 24] have highlighted the influence of the importance with which both negative and positive memories are perceived in posttraumatic growth. Moreover, Bernard et al. [23] found that the centrality given to positive events was associated with measures of adaptive functioning, such that the recovery of these memories could serve as a coping mechanism in difficult situations and probably help prevent the effects of stress.

Similarly, Contractor et al. [25] presented a proposal for approaching PTSD that advocates the incorporation of techniques that focus on positive autobiographical memories into trauma-focused treatments. This model was recently updated [26] and was tested in a pilot study [27], and the results showed that the narration of specific positive memories had beneficial impacts on the severity of PTSD symptoms. From this proposal, techniques focused on positive memories would have an effect on the reduction in the severity of PTSD in three ways: (1) direct effects on the severity of PTSD (e.g. through the increase in positive affect and the decrease in negative affect, the development of adaptive cognitions and the increase in the specificity of autobiographical memory), (2) increased effects of trauma-focused interventions (e.g. decreased fear of discussing memories related to trauma and increased preparedness to begin a trauma-focused intervention), and (3) effects on the ease and effectiveness of the processing of traumatic memories (i.e. through an increase in the availability of information and positive experiences that can help to modify the emotional structures related to the trauma, also replacing positive memory to trauma memory as the main point of reference and positively influencing identity and self-concept). Additionally, the incorporation of positive memories has a potential effect in reducing dropout rates (which is important in trauma-focused treatments) and improving treatment adherence and therapeutic alliance.

However, the effect of focusing on positive memories remains to be explored, and it is necessary to continue developing and evaluating intervention proposals focused on the processing of specific positive memories, which are conceived as complementary to trauma-focused interventions. Moreover, this type of proposal is an interesting alternative to solving some of the problems detected in the available interventions for the treatment of trauma in female survivors of IPV.

### Objectives

The *general objective* of the study is to develop and evaluate the efficacy and effectiveness of an evidence-based psychological intervention program focused on trauma that incorporates positive memories into treatment programs for women who have survived IPV. This general objective is divided into the following *specific objectives*:Design of an empirically validated psychological intervention program for women who have survived IPV and have posttraumatic symptoms that incorporates the approach of positive memories into a cognitive-behavioural treatment program focused on trauma.Application and evaluation of the effectiveness of the program focused on positive memories in women who have survived IPV and have posttraumatic symptoms, considering the following:Posttraumatic symptoms, including general posttraumatic symptoms and PTSD symptomsVariables associated with violence, including experience of violence (physical, sexual and psychological), acceptability of violence; victim blaming attitudes; and motivation for leaving the relationshipMeanings associated with trauma, including thoughts about the self, the world and the future; self-concept and identity; and centrality of traumaPositive and negative affect and regulation of positive and negative affectAssociated symptoms, including anxiety, depression, self-esteem, emotional dysregulation, and general health

To determine the efficacy, the following will be assessed:The effects achieved by the program focused on positive memories compared to a control group on the waiting listThe differential effects of the cognitive-behavioural treatment program with and without the incorporation of the module corresponding to the approach of positive memoriesThe effects achieved by the program focused on positive memories over time (considering follow-up periods of up to 1 year)The clinical significance of the changes obtained by the treatment(3)Evaluation of the implementation and effectiveness of the program, assessed through:Adherence to treatment (estimated by the rates of rejections, dropouts and fulfilment of tasks)The satisfaction of women with treatmentTherapists’ satisfaction with the treatment

The *complementary objective* of the project is the development and, where appropriate, translation and validation of instruments for the evaluation of the different variables considered in the study for which there are no versions and adaptations for the Spanish population.

## Methods/design

We used the SPIRIT reporting guidelines [28].

### Design

The design is a single-blind, randomized controlled trial (RCT) comparing two trauma-focused cognitive-behavioural treatment (with and without positive memories’ module) for female survivors of IPV and a wait-list condition (superiority trial). A multigroup design (3 groups) will be used with repeated measures with five levels (pretreatment, posttreatment and follow-ups of 3, 6 and 12 months) for the experimental groups and two levels (pre and post) for the control group. Consequently, the three treatment groups are as follows: (a) waiting list control group (WL), (b) cognitive-behavioural treatment (CBT), and (c) cognitive-behavioural treatment with a focus on positive memories (CBT-M +).

Assessors of treatment outcomes will be blinded to the experimental conditions. To avoid unplanned imbalances in the size of the three groups and a loss of statistical power, a block randomization procedure will be used.

### Setting

Participants will be recruited in community settings, specifically through several women's and IPV support organizations, institutions, and services around Madrid (Spain). Women who attend these centres for attention because of IPV will be referred by professionals and assessed to establish the eligibility criteria.

### Eligibility criteria

We adopt the WHO definition of IPV as ‘any behaviour within an intimate relationship that causes physical, psychological or sexual harm to those in the relationship’ [29]. Participants are eligible if they (1) are women; (2) are over 18 years old; (3) are proficient in the use of the Spanish language; (4) are or have been victims of IPV; (5) have experienced IPV at least one month before the start of the trial; (6) present symptoms of PTSD according to DSM-5 criteria as determined by the Global Assessment of Posttraumatic Stress Scale 5 (EGEP-5; in Spanish: Evaluación Global de Estrés Postraumático 5; Crespo et al. [30]); and (7) have voluntarily agreed to take part in the study.

Participants will be excluded if they (1) show suicide risk as assessed by item 9 (scores > 1) of the Spanish version of the Beck Depression Inventory II—BDI-II [31]; (2) present conditions that could prevent compliance with the treatment (namely, abuse of alcohol or drugs, cognitive impairment or illiteracy in Spanish); (3) have been diagnosed or suffer from psychotic disorders; and (4) have received trauma-focused treatment within the past 6 months.

### Sample size

To determine the target sample size, we considered the effect sizes found in the literature (specifically, the overall effect size—omnibus—calculated in the meta-analysis by Arroyo et al. [5]), which ranges from 0.71 to 1.33. Considering an alpha of 0.05 and a statistical power level of 0.80, a minimum group size of 31 was established. Taking a conservative estimate of the expected dropout rate of 30%, a sample size of 45 women per group will be the target, indicating a total of 135 participants across the 3 experimental conditions (CBT, CBT-M + and WL control group).

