In a second moment of the analysis of the changes over time, the changes between the pre, post and follow-ups will be analysed only for the two experimental groups. For this, an ANOVA will be applied for each of the outcome variables, including an intergroup factor (with two levels: CBT and CBT-M +) and an intrasubject or repeated measures factor, with five levels (i.e. pre, post, 3 months, 6 months and 12 months). In the application of these ANOVAs, the assumption of sphericity will be verified using the Mauchly test, and where appropriate, the Huynh-Feldt correction will be used. Likewise, ANCOVAs of one factor (type of treatment) will be performed for each outcome variable, using the value of the pretreatment evaluation as covariance.

To determine the differences between the two treatments, the intergroup differences and the interactions between time and type of treatment obtained in the different ANOVAs and ANCOVAs mentioned in the previous point will be addressed.

In all analyses, the Holm–Bonferroni correction will be used to adjust the level of significance for multiple comparisons.

To establish the clinical significance of the changes obtained, *χ*^2^ tests will be used considering the data relative to those variables that present a cut-off point capable of discriminating the clinical improvement of the participants. Likewise, the relative risk of presenting problems of one experimental group with respect to the other at different times of measurement will be calculated. In addition, the McNemar related proportions will be calculated to verify if the percentage of problems is the same or different in the pretreatment and in the different subsequent measurement moments, and the Jacobson-Truax method will be applied by calculating the index of reliable change. This analysis will be supplemented by the calculation of the effect size of each variable.

In the specific analysis of the reabuse or revictimization variables, it is expected that the scores show high asymmetry and kurtosis, so they will be recoded as dichotomous variables (presence vs. absence for each type of violence or abuse) in accordance with the procedure described by Johnson et al. [12].

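### The 80% power leaves out the planned Holm–Bonferroni correction and is not shown for CBT-M+ versus CBT, a central comparison with no stated effect size

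*Protocol article*

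**What the plan says.** The Sample size section of the protocol article contains one calculation. Its effect size is described as "the overall effect size—omnibus—calculated in the meta-analysis", and its value is given only as a span: "which ranges from 0.71 to 1.33". From this, "Considering an alpha of 0.05 and a statistical power level of 0.80, a minimum group size of 31 was established". The inflation follows: "Taking a conservative estimate of the expected dropout rate of 30%, a sample size of 45 women per group will be the target". Over three arms that makes 135 women. The section does not say which value in the range was used, which contrast or test it applies to, or whether the test is two-sided.

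The Abstract gives the aim: "The present study aims to test the effect of adding a positive memory module to trauma-focused CBT for female survivors of IPV". The Objectives list two between-group efficacy questions: CBT-M+ against wait-list, and the programme with against without the module. The CBT subsection of Interventions, with Table 1, makes CBT a time-matched active comparator, because neutral imagery fills the slots that CBT-M+ gives to positive memories. According to the Design section, wait-list is measured only before and after treatment.

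On multiplicity, the Statistical analysis section says: "In all analyses, the Holm–Bonferroni correction will be used to adjust the level of significance for multiple comparisons". The same section plans ANCOVAs that adjust for the pretreatment score, including pairwise ones.

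**The concern.** A power statement should describe the tests that will be run. Here it is made at alpha 0.05, while the analysis section adjusts for multiple comparisons in all analyses. The two sections therefore do not describe the same test.

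The effect size is also an overall effect from a meta-analysis. Used for CBT-M+ versus CBT, it would require the module to add as much over full, time-matched CBT as the quoted overall effect. The document gives no reason to expect this and no other effect for that contrast. Yet it is the comparison named in the Abstract and the Discussion, and the only randomised one left at 3, 6 and 12 months.

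The risk is in interpretation. A reader who takes 80% power to cover the add-on question could read a non-significant result as evidence that the module adds nothing, when a modest benefit would usually be missed.

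**Working it through.** **Inputs from the document.** Alpha 0.05; power 0.80; effect range 0.71 to 1.33; 31 evaluable and 45 recruited per arm; 30% dropout; three equal arms; Holm–Bonferroni; ANCOVA on the pretreatment score.

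**Assumptions, not in the document.** Two-sided tests; effects in SD units; pre-post correlation 0.5 where ANCOVA is used; Holm taken over the three pairwise contrasts of one outcome.

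**1. Reproducing 31 and 45.**
- Normal approximation: n = 2 × (1.960 + 0.842)² / 0.71² = 31.1 per group. Exact t power at n = 31 and d = 0.71 is 0.785 (0.798 by the normal approximation).
- Dropout: 31 / 0.70 = 44.3, rounded up to 45.
- A three-group F test with both active arms 0.71 above wait-list has f = 0.71 × √2 / 3 = 0.335 and power 0.82 at 31 per group, so that basis also fits.
- d = 1.33 needs only 9 to 10 per group, so the low end of the range fits the stated number and the high end does not.

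**2. Wait-list contrasts under Holm.** Simulated t-tests on unadjusted posttreatment scores, 31 per arm, Holm over three pairs, d = 0.71 for the contrast of interest:
- Other active arm also at 0.71: about 0.66 for each wait-list contrast.
- Other active arm at 1.33: about 0.755.
- For reference, if this contrast had to pass at the first Holm step (alpha 0.05/3), power would be 0.63.

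**3. CBT-M+ versus CBT.** No effect is stated, so a range is shown. The value 0.62 is 1.33 − 0.71, the widest gap that fits inside the quoted range. It is a generous illustration, not a planned effect. Exact t, two-sided 0.05. For ANCOVA, d is divided by √(1 − 0.5²) = 0.866.

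| Assumed d | 31 per arm, unadjusted score | 31 per arm, ANCOVA, r = 0.5 | 45 per arm, unadjusted score |
|---|---|---|---|
| 0.62 | 0.67 | 0.79 | 0.83 |
| 0.5 | 0.49 | 0.61 | 0.65 |
| 0.3 | 0.21 | 0.27 | 0.29 |

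With both ANCOVA at r = 0.5 and all 45 per arm analysed, d = 0.3 becomes 0.3 / 0.866 = 0.346, and power is 0.37.

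Under Holm at 31 per arm on unadjusted scores, simulated head-to-head power is about 0.65 with arm means (0, 0.71, 1.33) and about 0.18 with (0, 0.71, 1.01).

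**4. Detectable difference at 80% power, 31 per arm, alpha 0.05.** d = 0.72 on unadjusted scores. With ANCOVA at r = 0.5: 0.723 × 0.866 = 0.63.

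**The case against.** Much can be said for the plan, and some of it stands.

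- The stated arithmetic is sound. Both 31 and 45 reproduce, so the fault lies in what the figure is taken to cover.
- A reader might infer that head-to-head power cannot exceed about 0.67. The document does not support this. The planned ANCOVA could raise it (0.79 at d = 0.62 if the correlation is 0.5), and so could better retention than the 30% loss, which the plan itself calls conservative (0.83 if 45 per arm are analysed).
- A reader might also infer that the plan's own range implies 0.62 for CBT-M+ versus CBT. It does not. The plan assigns that contrast no effect and does not say what the ends of the range represent.
- Nor does it follow that 80% power holds only for a single unadjusted wait-list contrast. The three-group F test reaches 0.82 under the pattern above, and at d = 1.33 a wait-list contrast has power above 0.99 even at alpha 0.05/3. The document also does not say that the meta-analytic effect is against wait-list.
- The head-to-head is not the only aim, since the Objectives list the wait-list comparison first.
- No passage says that non-significance would be read as no added benefit, and effect sizes are already planned.

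These points limit the claim but do not remove it. A significant F test driven by wait-list says nothing about the module, and for modest add-on effects neither ANCOVA nor full retention brings power near 0.80.

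**Conclusion.** The concern holds in a limited form. The 80% figure fits an unadjusted comparison at d = 0.71. On unadjusted posttreatment scores it falls to about 0.66 to 0.75 per wait-list contrast under the plan's own Holm rule, if that rule is applied over three pairs. For CBT-M+ versus CBT the 80% is not shown, because no effect is stated. At 31 per arm and unadjusted alpha, power is 0.67, 0.49 and 0.21 at assumed differences of 0.62, 0.5 and 0.3, and the detectable difference is about 0.72, or 0.63 with ANCOVA at an assumed correlation of 0.5.

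These values depend on two-sided testing, SD-unit effects and independent observations. Treatment is delivered in groups of 6 to 8 women. Any within-group correlation would lower power further, but the document gives no value for it and none is used here.

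**What to change.** Revise the Sample size paragraph, leaving enrolment at 135:

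1. State the contrast or test, the effect size and the alpha (with sidedness) on which 31 per group rests.
2. Restate the power under the planned Holm–Bonferroni correction, naming the family of comparisons.
3. Give the detectable CBT-M+ versus CBT difference under the planned ANCOVA, with the assumed pre-post correlation and, where possible, its source.
4. In the Statistical analysis section, commit to reporting CBT-M+ versus CBT as an estimate with a 95% confidence interval, and say that a non-significant result will not be taken to show that the module adds nothing.

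The cost is text only. The stated power will look less favourable at the low end of the effect range.
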